##### Thoroughness of cleaning

Success or failure of environmental cleaning as measured by the removal of invisible gel dots will be examined using a GLMM with a binomial response (clean/not clean). This will model the probability of success as the number of successfully clean sites divided by the total number of sites marked.

The independent variables will be the intervention (yes/no) and the dot location (e.g., ICU, toilet). The model will include a random intercept for each hospital, which focuses the analysis on within-ward change by removing each wards underlying success rate. We will test two models with independent variables of:A simple binary intervention (yes/no)A linear intervention using the time since intervention (0, 1, 2, etc.)

The linear model allows for a gradual improvement in success rates. We will compare the fit of the two models using the Akaike Information Criterion [32].

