## Methods/design

### Study design

#### Stepped-wedge design

This is a randomised controlled trial using a cross-sectional stepped-wedge random allocation [12]. There will be sequential roll-out of an environmental cleaning bundle intervention to 11 Australian public and private hospitals over 62 weeks. Example trial timings are shown in Fig. 1.

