#### Power calculation

Eleven hospitals with a pre-intervention infection rate (a combination of SAB, CDI and VRE infections) of 5 per 10,000 patient days will give us 86 % power to detect a 20 % post-intervention reduction in infection risk. This is based on a two-sided 5 % significance level, a within-hospital correlation in infection rates of 0.3 and the intervention timings shown in Fig. 1. The pre-intervention infection rate and within-hospital correlation were estimated using a dataset of over two million hospital admissions and infection data from nine Queensland hospitals [28]. The stepped-wedge sample size formula is from Hussey and Hughes [29]. We assumed no delay in the treatment effect for the sample size calculation, that is, rates decline as soon as the intervention begins.

To detect an increase in the secondary outcome (thoroughness of cleaning) from 82 to 87 % due to the intervention with a 92 % power requires only five hospitals with 40 observations per hospital per 4 weeks. This is based on the pilot data and recent studies [17, 22, 30, 31]. This secondary hypothesis requires far fewer hospitals because the outcome of cleaning failure is likely to be more common than HAIs (primary outcome), which are relatively rare.

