#### Analysis

##### Infection rates

Infection rates will be analysed using Poisson regression with the infection counts as the dependent variable and the weekly number of patient days as the denominator. The key independent variable will be the intervention (yes/no). The intervention variable will switch from “no” to “yes” after the first full month of the intervention. The model will include a linear term for calendar time to control for any long-term pattern in infection rates. It will be a generalised linear mixed model (GLMM) with a random intercept for each hospital [29].

The characteristics of the hospital (e.g. size) will not be independent variables as these should remain roughly constant throughout the study. We will test the residuals of the model to look for autocorrelation over time and will check for influential observations. In a sensitivity analysis we will consider the possibility of a delayed intervention effect of up to one month. This is plausible because it may take time for the intervention to break the cycle of infection transmission.

The primary outcome will be a fixed effect meta-analysis of the estimated change in infection rates across the three infection types. We will use a forest plot to visually examine the variation in the change in infection rates. The combined mean will be considered statistically significant if the 95 % confidence limit does not include zero. The meta-analytic approach avoids using a combined infection rate, as this is questionable given the different drivers of infection. However, it will still give an overall estimate of the interventions impact on HAIs.

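### The thoroughness-of-cleaning models omit calendar time, so part of any background trend is attributed to the bundle; the 92% power figure should be restated with time adjustment

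*Protocol article*

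**What the plan says.** All places are in the protocol article.

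- Analysis, Thoroughness of cleaning, gives the covariates: "The independent variables will be the intervention (yes/no) and the dot location (e.g., ICU, toilet"). It adds: "The model will include a random intercept for each hospital". Two models are compared by AIC. They differ only in the intervention term, which is either binary or "A linear intervention using the time since intervention (0, 1, 2, etc".). Neither contains calendar time.
- Analysis, Infection rates, does contain it: "The model will include a linear term for calendar time to control for any long-term pattern in infection rates".
- Power calculation says that detecting a rise "from 82 to 87 % due to the intervention with a 92 % power" "requires only five hospitals with 40 observations per hospital per 4 weeks". The correlation and the citation of the stepped-wedge formula belong to the infection calculation: "This is based on a two-sided 5 % significance level, a within-hospital correlation in infection rates of 0.3". No correlation, set of start weeks or time adjustment is given for the cleaning figure.
- Stepped-wedge design: "11 Australian public and private hospitals over 62 weeks", with intervention lengths of 20 to 50 weeks.
- Randomisation describes a control phase of 8 weeks of baseline data collection before each hospital's start. The section on the secondary outcome places audits in the control and intervention periods.

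**The concern.** In a stepped wedge every hospital moves from control to intervention and never back, so exposure rises with calendar time. Randomised start dates allow the two to be separated, but only if the model contains time. Without it, a hospital intercept plus an intervention indicator gives a pooled before-after contrast. A general improvement in cleaning over the study would then appear as a bundle effect.

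The article lists the covariates, and the neighbouring infection model has the term. This is therefore a stated specification that differs between two outcomes of one trial, not a detail left to an analysis plan. Thoroughness is the outcome that Table 2 labels secondary, it has its own power statement, and it is the direct measure of whether the bundle changed cleaning. The primary infection analysis is not affected.

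**Working it through.** **Inputs.** From the article: 82% to 87% (difference 0.05, mean 0.845, variance 0.845 × 0.155 = 0.1310); 40 observations per 4 weeks, i.e. 10 per week per hospital; 62 weeks; intervention lengths of 20–50 weeks, so starts after week c = 12 to 42. Assumed: starts every 3 weeks (12, 15, …, 42), because Fig. 1 is not visible; two-sided 5%, carried over from the primary outcome; cleaning correlation 0 to 0.3; audits either in all pre-intervention weeks or in the 8 baseline weeks only.

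**1. The stated 92%.** A two-proportion comparison with n per condition has power Φ[(0.05 − 1.96√(2 × 0.1310/n)) / √((0.1476 + 0.1131)/n)]. With n = 1200 this is Φ[(0.05 − 0.02896)/0.01474] = Φ(1.43) = 92.3%.

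For the wedge without a time term, the within-hospital information is 10 × Σ c(62 − c)/62. Five evenly spread starts (12, 19, 27, 35, 42) give 9.68 + 13.18 + 15.24 + 15.24 + 13.55 = 66.89. SE = √(0.1310/668.9) = 0.0140, and power = Φ(0.05/0.0140 − 1.96) = 95%. Over all 462 choices of five starts it is 93–97%. So 92% is approximately reproduced (92–97%).

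**2. Add linear time.** The product sum of time and exposure is 31 × 66.89 = 2073.5. The within-hospital time sum of squares is 5 × (62³ − 62)/12 = 99,277.5. Remaining information: 66.89 − 2073.5²/99,277.5 = 23.58. SE = √(0.1310/235.8) = 0.0236, and power = Φ(2.12 − 1.96) = 56%. For 11 hospitals the information falls from 151.69 to 50.45, and power = Φ(3.10 − 1.96) = 87%.

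Ranges over correlation 0–0.3 and, for five hospitals, all choices of starts:

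| | Audits in all pre-intervention weeks | 8 baseline weeks only |
|---|---|---|
| 5 hospitals, no time term | 93–97% | 67–72% |
| 5 hospitals, linear time | 50–77% | 39–59% |
| 5 hospitals, 4-week period effects | 31–73% | 28–52% |
| 11 hospitals, linear time | 87–95% | 81–87% |
| 11 hospitals, 4-week period effects | 83–93% | 75–84% |

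No five-hospital variant with a time term reaches 92%.

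**3. How much of a trend enters the estimate.** With audits in all weeks, the mean intervention week is 31 weeks after the mean control week in every hospital, whatever c is. A trend of b points per year therefore adds about 31b/52 = 0.60b. With 8 baseline weeks the gap is 4 + (62 − c)/2, i.e. 29 weeks at c = 12 and 14 at c = 42. The information-weighted mean is 21.8 weeks, or 0.42b. Random-intercept fits at low correlation give slightly less: 2.9 and 2.0 points for b = 5, i.e. 58% and 40%.

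**4. False-positive rate, 11 hospitals, no bundle effect.** SE = √(0.1476/1516.9) = 0.99 points (all weeks) or √(0.1476/707.5) = 1.44 points (8 weeks). The rate is Φ(bias/SE − 1.96) plus the small opposite tail. For b = 5 with all weeks: Φ(2.98/0.99 − 1.96) ≈ 86%. The last two columns span this hand calculation, the random-intercept calculation and logistic simulations.

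| Assumed trend, points/year | Hand calculation: all weeks / 8 weeks | Range, all weeks | Range, 8 weeks |
|---|---|---|---|
| 2 | 23% / 9% | 21–24% | 8–9% |
| 3 | 44% / 14% | 44–48% | 14–18% |
| 5 | 86% / 31% | 82–92% | 28–38% |

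The spurious odds ratios are about 1.09, 1.14 and 1.26 (all weeks) and 1.06, 1.10 and 1.18 (8 weeks). Adding linear calendar time brought the rejection rate back close to 5% in each case.

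**5. The time-since-intervention model.** In simulation its false-positive rates at 2, 3 and 5 points per year were about 26–27%, 51–59% and 95–96% (all weeks), and 15–16%, 24–35% and 70–75% (8 weeks). AIC chose it in 54–69% of runs with all weeks and 60–84% with 8 weeks, against about 46–50% with no trend.

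**The case against.** **No trend is documented.** This stands: 2 to 5 points per year is assumed. Under Limitations, sites agree not to change cleaning policy or products without agreement and are monitored frequently. Cleaners do not know dot positions or audit timing, and feedback belongs to the intervention period. These safeguards make drift less likely, but the same section names seasonal, organisational and policy changes as possible limitations.

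**The audit schedule matters.** This also stands. On the 8-week reading of Randomisation the bias and false-positive rates are much smaller, so both readings are shown.

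**Calendar time is not a complete cure.** If audits begin 8 weeks before each hospital's own changeover, effects of being audited follow hospital time, and a common calendar term would not fully remove them. That limits the fix but does not justify leaving time out.

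A reader might infer four stronger things that the document does not support:

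- That the whole of any secular change is credited to the bundle. Only part of it is (working, step 3).
- That time since intervention is merely shifted calendar time, so AIC must select it under a trend. On the natural reading it stays at zero through the control phase and rises only afterwards, so AIC leans towards it without always choosing it.
- That the 92% is shown to be wrong, or to follow simply from ignoring time. Its inputs are not given, and on the 8-week schedule five hospitals reach only 67–72% even unadjusted.
- That the trial is underpowered for cleaning, or that this is its one confirmatory secondary outcome. Eleven hospitals are enrolled, the article does not use that label, and the abstract lists three secondary outcomes.

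**Conclusion.** The concern holds for the missing calendar-time term. As written, both cleaning models attribute part of any background trend to the bundle, and the type I error is inflated on either audit schedule. It is strongly so if audits run throughout the control period and the trend is as large as 5 points per year. Bias is the main consequence.

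Power is secondary and conditional. Approximate reproduction of 92% required both no time term and audits in all pre-intervention weeks. With a time term the five-hospital statement fails under every variant tried, while the 11 enrolled hospitals retain about 75–95%. These sizes rest on the assumed start weeks, correlation, audit schedule and trends. The direction of the bias does not: it follows from control always preceding intervention.

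**What to change.** Add calendar time to both thoroughness models: at least the linear term already used for infections, or 4-week period effects. Test the intervention term adjusted for it, and make the AIC comparison between the two adjusted models. Replace the five-hospital power statement with one for the 11 enrolled hospitals under the time-adjusted model, stating the within-hospital correlation for cleaning, the start weeks, and whether audits cover the whole control period or only the 8 baseline weeks.

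The change adds one covariate (or one set of period effects) and needs no new data. The cost is a wider standard error and a less favourable stated power. In the 11-hospital linear-time example with audits in all weeks, the standard error rises by a factor of √(151.69/50.45) ≈ 1.7.

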##### Bio-burden of high touch surfaces

The total amount of ATP, both microbial and non-microbial, will be quantified and expressed as relative light units. This will be correlated with the secondary outcome data (thoroughness of cleaning).

##### Changes in staff knowledge and attitudes

Several pre-existing scales from the literature will be used to assess both the attitudes and knowledge of environmental cleaning staff [33–36]. Paired *t* tests (or Wilcoxon signed-rank tests) will be used to analyse the changes in attitudes between the pre- and post-intervention phases. Change in knowledge will be assessed as the difference in the proportion of correct responses at time 1 versus time 2, tested using McNemar’s test. General perceived organisational support will also be assessed in a short eight-item measure [37].

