### Outcomes and data collection: objective 1: effectiveness of the environmental cleaning bundle

Objective 1 outcomes and measures are shown in Table 2.

**Table 2 Tab2:** Objective 1 outcomes and measures

Outcome	Measure	Method
Primary outcome		
Healthcare-associated infection (HAI) rates in each trial site	Numbers of *Staphylococcus aureus* bacteraemia (SAB), *Clostridium difficile* infection (CDI) and clinical isolates of vancomycin resistant enterococci (VRE) and monthly rates per 10,000 occupied bed days	Datasets include all patients across the hospital with a HAI, and data on occupied bed days Collated from: - Hospital infection data and reports for ongoing surveillance - Hospital occupied bed days reports
Secondary outcome		
Hospital cleaning performance—thoroughness of hospital cleaning in each trial site	Number and percentage of ultraviolet (UV) gel dots removed completely following cleaning	DAZO® Fluorescent Marking Gel dots applied to frequent touch sites around two patient cubicle and bathroom areas in the intensive care unit (ICU) and the highest risk wards
Other outcomes—study specific data set		
Bio-burden of frequent touch surfaces post cleaning	Levels of organic matter in relative light units (RLUs) post cleaning in three hospitals	Adenosine tri-phosphate (ATP) bioluminescence measurements
Other outcomes—study specific data set		
Changes in staff knowledge and attitudes around environmental cleaning	Pre-intervention educational needs. Pre- and post-intervention knowledge and attitudes about environmental cleaning and job roles	Environmental services staff questionnaires and discussion groups
Other outcomes—existing data set		
Changes in rates of screening and clinical isolates	Numbers of positive clinical isolates of other multi-resistant organisms per 1000 patient days at risk	Collated from hospital infection data and reports, where available for ongoing surveillance and supplied to project team by trial site team
Other outcomes—existing data set		
Changes in patients’ perception of hospital cleanliness	Patients’ perceptions of cleanliness	Collated from existing hospital-based survey data, where available and supplied to project team by trial site team

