##### Knowledge and attitudes of environmental cleaning staff

The knowledge and attitudes of environmental cleaning staff will be surveyed pre- and post-intervention and will serve two purposes. First, it will provide an understanding of baseline hospital context, including knowledge, attitudes and practices of environmental services staff, which will be used to tailor the educational component of the cleaning bundle. Second, it will allow a comparison of knowledge and attitudes about environmental cleaning between the pre- and post-intervention phases. This is particularly important to gauge whether the bundle has impacted not only upon behaviour but also on attitudes and knowledge, which are the longer-term drivers of behavioural outcomes.

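### Knowledge change is a proportion of correct responses on scales but is tested with McNemar's test, and the unit of analysis is not fixed, so no single valid test of overall knowledge is specified

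*Protocol article*

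**What the plan says.** The analysis section on changes in staff knowledge and attitudes describes the instruments thus: "Several pre-existing scales from the literature will be used to assess both the attitudes and knowledge of environmental cleaning staff". The two constructs are then analysed differently. For attitudes, paired *t* "tests (or Wilcoxon signed-rank tests) will be used to analyse the changes in attitudes between the pre- and post-intervention phases". For knowledge, "Change in knowledge will be assessed as the difference in the proportion of correct responses at time 1 versus time 2, tested using" McNemar's test.

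The only item count in that section belongs to another construct: "General perceived organisational support will also be assessed in a short eight-item measure". For knowledge the article gives no number of items, no pass mark, and no statement of whether the proportion is taken over staff for one item, over items within one person, or over all answers together.

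Elsewhere knowledge is treated as one thing to be compared before and after. Table 2 gives the measure as "Pre- and post-intervention knowledge and attitudes about environmental cleaning and job roles", and the data-collection section says "The knowledge and attitudes of environmental cleaning staff will be surveyed pre- and post-intervention and will serve two purposes", the second purpose being the pre/post comparison. Table 2 places the outcome under other outcomes; the abstract counts it among the secondary outcomes of objective one.

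**The concern.** McNemar's test compares the two kinds of discordant pair, right-then-wrong and wrong-then-right. Its reference distribution assumes that each pair comes from a different, independent person. The stated quantity is a proportion of responses, and the instruments are scales, so each cleaner most likely contributes several pairs. The outcome and the test then meet only if something further is decided, and the article does not decide it.

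Two ways of carrying out the plan follow naturally:

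- **Item by item.** Each test is sound, but the result is a list of item findings. There is no single answer to whether knowledge changed, which is the question Table 2 poses.
- **Pooled over items.** There is a single answer, but a cleaner who learned (or forgot) tends to move on several items together. The test ignores this, so its standard error can be too small and a chance difference can be declared a change in knowledge.

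At stake is whether the trial can make a sound statement that the bundle changed staff knowledge. The infection result is not affected.

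**Working it through.** **Plan's own figure.** There is none to reproduce. The power section covers infections and cleaning thoroughness only. Its significance level ("This is based on a two-sided 5 % significance level") is stated for the infection calculation; I assume the same 5% for knowledge.

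**Inputs.** All are assumptions, since the article gives none for knowledge: *k* = 5, 10 or 20 items; 100 or 300 paired cleaners; person-level ability with SD 1 logit; a person-specific change with mean zero and SD 0, 0.5 or 1.0 logit. The mean change is zero, so every rejection is a false positive.

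**Why pooling can fail.** Let D = +1, 0 or -1 for each person-item pair (gained, unchanged, lost). McNemar's statistic is (b - c)²/(b + c), with b and c the two discordant counts. Its denominator estimates the variance of the sum of D as if all pairs were independent. If changes on two items by the same person have correlation ρ, the true variance is larger by

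F = 1 + (k - 1)ρ,

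and the actual two-sided error is 2[1 - Φ(1.96/√F)].

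**Value of ρ.** With p₁ and p₂ a person's chances of a correct answer at the two times, ρ = Var(p₂ - p₁)/E[p₁(1 - p₂) + p₂(1 - p₁)]. Take a common item level of 1 logit and split the change evenly over the two occasions. Numerical integration then gives:

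- SD 0: ρ = 0
- SD 0.5: ρ = 0.00872/0.3624 = 0.024
- SD 1.0: ρ = 0.0333/0.3807 = 0.087

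**Example, 20 items.** SD 0.5: F = 1 + 19 × 0.024 = 1.46, 1.96/√1.46 = 1.62, error 10.4%. SD 1.0: F = 1 + 19 × 0.0874 = 2.66, 1.96/√2.66 = 1.20, error 23%.

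**Simulation.** Two simulations were run. Simulation A: 2,000 data sets per cell, 300 cleaners, item levels varying with mean 0.8 and SD 0.7 logit. Simulation B: 4,000 data sets per cell, 100 and 300 cleaners, common item level of 1 logit. Type I error of the pooled McNemar test:

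| Items | Change SD | Formula | Simulation A | Simulation B |
|---|---|---|---|---|
| 5 | 0.5 | 6.1% | 6.8% | 6.1-6.2% |
| 5 | 1.0 | 9.2% | 10.0% | 8.7-9.2% |
| 10 | 0.5 | 7.6% | 7.5% | 7.2-7.4% |
| 10 | 1.0 | 14.3% | 14.0% | 13.5-14.2% |
| 20 | 0.5 | 10.4% | 10.6% | 10.4% |
| 20 | 1.0 | 23.0% | 22.1% | 22.6-24.3% |
| any | 0 | 5.0% | not run | 4.4-5.1% |

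**Alternatives under the same conditions.** McNemar's test on one item: 4.3-5.9% (simulation B). Paired *t* test on each cleaner's proportion correct: 4.5-5.5% in simulation B and 4.8-5.9% in simulation A. Both stay near 5% whatever the change SD.

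**The case against.** The strongest reply is that the sentence has a sound reading. A proportion of correct responses can mean the share of staff who answer a given question correctly, before and after, and McNemar's test is the standard test for that. The authors do separate scored attitudes from right/wrong knowledge answers, and item-level results suit the survey's first purpose, which is to tailor the training. All of this stands.

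A reader might therefore infer too much in three places:

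- **That the planned test is invalid on any reading.** The text does not support this. A single-item test holds its level, and so would one pass/fail classification per cleaner. The article defines no pass mark, however, and pass/fail is not the stated quantity.
- **That pooling will be done, and that it must inflate the error.** Nothing in the article says responses will be pooled, and without person-to-person differences in change the pooled test holds 5%. Such differences are plausible, since the training is tailored to site and role, but their size is unknown.
- **That item-by-item testing carries a false-positive risk of 23%, 40% or 64%** for 5, 10 or 20 items, from 1 - 0.95^k. These figures need independent items and no correction. Items that move together would generally give a lower risk. The article does not say the tests will go uncorrected, and it may fairly leave that to an analysis plan for an outcome listed under other outcomes. I do not count them in the size of this point.

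What the reply does not remove is that outcome and test are both named, the unit that would join them is not, and even the sound item reading yields no test of knowledge as a whole.

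**Conclusion.** The point holds as a poor fit between a stated outcome and a stated test, with the unit of analysis left open. It does not show that the authors chose a wrong test for a single item.

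On the item reading, the loss is the absence of one test of overall knowledge. On the pooled reading, a nominal 5% test has a true level of about 6-10%, 7-14% or 10-24% for 5, 10 or 20 items if the change SD is 0.5 to 1.0 logit, and 5% if it is 0. That several knowledge items exist is itself an inference from the words scales and responses. The calculations also treat cleaners as independent of one another and do not examine clustering by hospital.

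The importance is low. The outcome is non-primary, has no power calculation or success criterion, and has no bearing on the infection analysis.

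**What to change.** In the section on changes in staff knowledge and attitudes, define the knowledge outcome as each cleaner's proportion of knowledge items correct. Test the change with the paired *t* or Wilcoxon signed-rank test that the section already plans for attitudes. A binomial mixed model for items correct, with person effects on both level and change, is an acceptable alternative; a person effect on level alone would not address the correlation in change. Keep McNemar's test for single items and label those results descriptive.

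The cost is a change of wording. No new data, sample size or survey design is needed. According to the trial status section, sites were still being recruited and randomisation had not taken place, so at that stage the change could be made before any outcome was seen.
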